#### Analysis strategy

The analysis will be per intent to treat. First we will compare the intervention group with the control group in order to verify that there are no significant differences between the two groups (socio-demographic characteristics, clinical baseline data, etc). We will use the mean (standard deviation) in the continuous variables and percentages in the categorical variables. For comparisons we will use the Student-t test for continuous variables and the Chi-squared test for categorical variables. Non-parametric tests may also be used.

The main variables of the result are the percentage of patients with tobacco cessation (patient's self-declared abstinence, expired air carbon monoxide levels, self-administered Minnesota tobacco abstinence symptoms, and cotinine levels in saliva), and tobacco dependence (Fagerström test for Nicotine Dependence scoring) at 1-year.

Process variables include severity of the depression (Zung Self-Rating Depression Scale), anxiety trait and state (STAI), impulsivity (Plutchik Impulsivity Scale), and efficacy self-perception (visual analogue scale).

We will use the general linear models of the SPSS 15 statistical package, to analyse the effect of the treatment on the categorical result variables (tobacco cessation rate). We will use the analyses of linear mixed models to analyse the effect of the continuous process variables (depression, anxiety, impulsivity and efficacy).

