**Method/design:**

*Design: *A randomised, controlled trial involving two groups, one of which is the control group consisting of patients on the standard pharmacological treatment for tobacco cessation (NST) and the other is the intervention group consisting of patients on topiramate as pharmacological treatment.

*Setting: *29 primary care health centres in the city of Zaragoza, Spain.

*Sample: *180 patients, aged 18–65 years, diagnosed with major depression, smoke more than 20 cigarettes/day, who have voluntarily asked for tobacco cessation therapy.

*Intervention: *A multi-component programme for tobacco cessation is offered to all of the patients in the study. This programme is made up of pharmacological therapy + group cognitive-behavioural therapy. Pharmacological therapy consists of NST for the control group and topiramate (200 mg/day) for the intervention group. Psychological therapy is made up of 16 sessions of manualised group therapy.

*Measurements: *Cessation will be assessed by patient self-declared abstinence, expired air carbon monoxide levels, and cotinine levels in saliva. Questionnaires on tobacco dependence, anxiety, depression, impulsiveness and self-efficacy will be administered. The interviewers will not know which group the patient belongs to (blind). The assessments will be carried out at baseline, D (cessation day) -1, D+1, weeks 1, 2, 3, 4, 6, 8, 10 and 13, and months 4, 5, 6, 8, 10 and 12.

*Main variables: *Tobacco cessation rates and tobacco dependence.

*Analysis: *The analysis will be per intent to treat. We will use the general linear models of the SPSS version 15 statistical package, to analyse the effect of the treatment on the result variable (tobacco cessation rate).

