##### Main outcome variables

In accordance with the aims of the study, the major outcome is tobacco cessation in patients with depression. The diagnosis of tobacco dependence will be made with the Spanish version of the MINI psychiatric interview substance dependence module adapted to tobacco [24]. This modification has been validated on a Spanish population with adequate psychometric properties [19]. Tobacco abstinence will be diagnosed by self-declared abstinence, self-administered Minnesota tobacco abstinence symptoms [25], expired air carbon monoxide [26], and cotinine in saliva. Tobacco abstinence, according to majoritarily-accepted criteria [27], has been defined using 2 concepts: 1. Occasional abstinence: In a follow-up visit, patients affirm that they have been abstinent, their levels of expired air carbon monoxide < 10 ppm, and cotinine levels in saliva < 5 ng/ml. Continuous abstinence: As of the visit at 30 days, patients affirm that they were abstinent the month before, expired air carbon monoxide levels < 10 ppm and cotinine levels in saliva < 5 ng/ml. Tobacco relapse will be diagnosed with the MINI psychiatric interview substance dependence module adapted to tobacco [24].

The diagnosis of depressive disorder will be made with the Spanish version of the MINI psychiatric interview, depression module [24], and the severity of the depression with the Spanish version of the Zung Self-Rating Depression Scale [22]. Recruitment will only include patients with depressive disorder and Zung scale scores < 60, which implies minimal to mild depression [22]. MINI psychiatric interview depression module [24], will be also used as criteria for depression relapse.

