##### Secondary variables

-The following socio-demographic data will be collected: sex, age, marital status (single, married/relationship, separated/divorced, and widowed), education (no studies, primary, lower secondary, upper secondary, university), occupation and social class (I, II, IIIN, IIIM, IV and V of the British Registrar General's Scale) [28].

-Tobacco dependence as measured by the Spanish version of the Fagerström test for Nicotine Dependence [29].

-Anxiety trait and state as measured by the Spanish version of the State-Trait Anxiety Inventory (STAI) [30].

-Impulsivity as measured by the Spanish version of the Plutchik Impulsivity Scale [31].

-Visual analogue scale for efficacy self-perception (range 0–10).

-Pharmacological side-effect events from the medical record.

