### Statistical methods

#### Sample size

To calculate the sample size we consider the tobacco cessation rate at 1 year follow-up as the main outcome variable. On the basis of published research data [5,6], we assume that this will be 35% in the control (NST) group, and we aim to detect a difference of 25% or more between any of the two groups (control and intervention). Published studies place placebo response at 10% [32]. Accepting an alpha risk of 0.05 and a beta risk of < 0.20 in a bilateral contrast, we would need 90 patients in each group [33].

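### The main outcome is stated inconsistently: the 1-year Fagerström score is main in one section and secondary in another, and withdrawal symptoms are listed under cessation but are absent from both formal definitions

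*Protocol article*

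**What the plan says.** **Status of the Fagerström score.**

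- Analysis strategy: the main result variables are the percentage of patients who stop smoking "and tobacco dependence (Fagerström test for Nicotine Dependence scoring) at 1-year".
- Abstract, Main variables: "Tobacco cessation rates and tobacco dependence". The instrument is not named here.
- Secondary variables: "Tobacco dependence as measured by the Spanish version of the Fagerström test for Nicotine Dependence".
- Main outcome variables: "the major outcome is tobacco cessation in patients with depression".
- Sample size: "we consider the tobacco cessation rate at 1 year follow-up as the main outcome variable".

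**Elements of cessation.**

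- Main outcome variables, general sentence: "Tobacco abstinence will be diagnosed by self-declared abstinence, self-administered Minnesota tobacco abstinence symptoms", followed by carbon monoxide and cotinine.
- Analysis strategy: the bracket that describes cessation includes "self-administered Minnesota tobacco abstinence symptoms, and cotinine levels in saliva), and tobacco dependence".
- Main outcome variables, the two formal definitions (occasional and continuous abstinence): self-report, carbon monoxide below 10 ppm and cotinine below 5 ng/ml. Neither mentions the Minnesota scale, and no threshold for that scale appears anywhere in the article.

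**The concern.** A trial needs one outcome, defined one way, on which its conclusion rests. Here the same score sits in two tiers, and cessation is described once with four elements and once with three. An analysis plan cannot follow both Analysis strategy and Secondary variables on the Fagerström score. It cannot apply the four-element version of cessation at all without inventing a cut-off.

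Two things are at stake. First, with two main variables and no rule linking them, a favourable result on either could be reported as the trial's main result. Second, a four-element and a three-element rule can classify the same patient differently, so the 1-year cessation rate could depend on a choice made after the data are seen.

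A further difficulty would arise if the Fagerström score were kept as a main variable and analysed only in patients still smoking. Those patients are selected by the other main outcome, so the comparison would no longer be between the groups as randomised.

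**Working it through.** **1. The passages side by side**

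| Section of the article | Fagerström score | Minnesota symptoms |
|---|---|---|
| Abstract | tobacco dependence is main; instrument not named | not mentioned |
| Main outcome variables, general text | not mentioned; cessation is the major outcome | listed among the means of diagnosing abstinence |
| Main outcome variables, two definitions | not mentioned | not part of either definition |
| Secondary variables | secondary | not listed |
| Sample size | not mentioned; 1-year cessation is the main outcome | not mentioned |
| Analysis strategy | main, at 1 year | listed inside the description of cessation |

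The conflict between Analysis strategy and Secondary variables is explicit and does not need the abstract. The conflict over the Minnesota scale exists even within Main outcome variables, between its general sentence and its two definitions.

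**2. The plan's own figure**

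Inputs from Sample size: 35% in the control group, a difference of 25 percentage points, two-sided alpha 0.05, beta below 0.20, 90 per group. With p1 = 0.35, p2 = 0.60 and mean 0.475,

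n = [z(α/2)·√(2 × 0.475 × 0.525) + z(β)·√(0.35 × 0.65 + 0.60 × 0.40)]² / 0.25²

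- Power 0.80: (1.960 × 0.706 + 0.842 × 0.684)² / 0.0625 = 61.4, so 62 per group, or 70 with continuity correction.
- Power 0.90: (1.960 × 0.706 + 1.282 × 0.684)² / 0.0625 = 81.8, so 82 per group, or 90 with continuity correction.

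The stated 90 is therefore not the minimum for beta of exactly 0.20, but it meets beta below 0.20. Without continuity correction, 90 per group gives 92.6% power for 35% versus 60%, and 98.4% for 35% versus 10%. This calculation concerns cessation only, so making cessation the sole primary outcome leaves it unchanged.

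**3. Error rate if both variables were primary**

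Assumption, not stated in the protocol: each is tested at 5% and either suffices.

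- Upper bound for any correlation: 0.05 + 0.05 = 0.10.
- Under independence: 1 − 0.95² = 0.0975.
- If the two tests always agreed: 0.05.

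The range is 5% to 10%. The two variables are likely to be related, so the value would lie below the bound. If both were kept and cessation were tested at 0.025, it would need 75 per group for 80% power (83 with continuity correction). The planned 90 would give 87.6%.

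**4. Quitters left out if the Fagerström score were analysed in continuing smokers only**

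The protocol does not say that it will be. With 90 per group and the rates in Sample size:

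| Cessation, control vs topiramate | Quitters left out | Smokers remaining, control vs topiramate |
|---|---|---|
| 35% vs 10% | 31.5 + 9 = 40.5, about 41 of 180 | 58.5 vs 81 |
| 35% vs 35% | 31.5 + 31.5 = 63 of 180 | 58.5 vs 58.5 |
| 35% vs 60% | 31.5 + 54 = 85.5, about 86 of 180 | 58.5 vs 36 |

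The exclusion is unequal between arms whenever the treatments differ in cessation.

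**The case against.** The intended hierarchy can largely be recovered. Main outcome variables and Sample size name cessation, the aims are framed as cessation at 1 year, and the only stated alpha belongs to cessation. Analysis strategy assigns a treatment-effect model to the cessation rate and mixed models to depression, anxiety, impulsivity and self-efficacy, but none to the Fagerström score. The Secondary variables list also holds age, sex and social class, so it reads partly as a list of other measurements. On the Minnesota scale, a measure without a cut-off cannot act as a pass/fail criterion, so the four-item lists may simply name instruments, as Table 1 does.

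Most of this stands, and it limits the consequences. It does not remove the contradiction, because Analysis strategy says outright that the Fagerström score is a main variable.

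Four stronger readings are tempting but not supported:

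- *That the trial plans to claim success on either variable.* No such rule is written; the text only fails to exclude it.
- *That the Fagerström score will be compared in smokers only.* Table 1 schedules it without that restriction, and the analysis is by intention to treat. How quitters are scored may be settled in a plan not shown.
- *That a symptom criterion would misclassify true quitters at month 12.* The Background says that patients with depression have more abstinence symptoms, but nothing shows how far these persist at 1 year.
- *That the sample size is wrong.* It is adequate for cessation.

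**Conclusion.** The point holds as a contradiction in the text about the main outcome, and it should be resolved before analysis. The Fagerström score is explicitly both main and secondary. The Minnesota scale is listed under cessation twice, defined into it nowhere, and has no cut-off.

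The size is moderate. The family-wise error is at most 10%, on the assumption that both variables are tested at 5% with either sufficient, and it falls towards 5% as their correlation rises. The 41 to 86 excluded quitters apply only under a smokers-only analysis that the plan does not specify, and they rest on the rates in Sample size. The effect of the two cessation rules on the 1-year rate cannot be calculated, because no Minnesota threshold exists to apply.

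Confidence is high for the conflicts in wording and lower for any effect on the result.

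**What to change.** 1. State one primary outcome: biochemically verified cessation at month 12, by self-report, carbon monoxide and cotinine as in Main outcome variables. Say which of the two definitions, occasional or continuous abstinence, it is. Both use these three elements, so naming the elements alone does not settle the matter.
2. Remove the Minnesota scale from the cessation lists in Main outcome variables and Analysis strategy. Add it to Secondary variables as a withdrawal-symptom score.
3. Move the 12-month Fagerström score to secondary in the abstract and Analysis strategy, in line with Secondary variables.
4. Use the baseline Fagerström score, already collected according to Table 1, as a covariate in the cessation model.

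If the sponsor prefers to keep both variables as main, a multiplicity rule must be stated instead.

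The cost is wording and one model term. No visit, measurement, treatment or sample size changes. The Fagerström result loses its main status.

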**Figure 1 F1:**
[figure not shown]
Flowchart: randomisation, sampling and monitoring of patients.

1. Tobacco cessation standard treatment with NST (control group) and

2. Tobacco cessation treatment with topiramate (intervention group).

The evaluation of the treatment outcomes will be performed at patient level and they will be assessed individually.

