### Randomisation, allocation and masking of study groups

Each patient will be allocated to either the intervention or the control group using a computer-generated random number sequence. The allocation will be carried out by an independent person, belonging to REDIAPP (Research Network on Preventative Activities and Health Promotion), who is not involved in the study. The method used to implement the random allocation sequence will be a central telephone. The sequence will be concealed until interventions are assigned. Patients agree to participate before the random allocation and without knowing which treatment they will be allocated to. Pharmacological treatment will be administered by a psychiatrist ([name]). Study personnel conducting psychological intervention and assessments ([name]) will be masked to participants' treatment conditions.

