### Intervention

#### Psychological intervention in both groups

A multi-component programme for tobacco cessation is offered to all of the patients in the study. This is made up of pharmacological therapy + group cognitive-behavioural therapy. The group is made up of 7–12 patients with depression and tobacco dependence, and is led by 2 therapists (a psychologist and a family doctor) trained in group therapy and tobacco cessation. Each session lasts 90 min., and the structure of every session and the contents are manualised and based on the standard programmes of this type [19]. It consists of 16 follow-up sessions: D (cessation day) -1, D +1, weeks 1, 2, 3, 4, 6, 8, 10 and 13, and months 4, 5, 6, 8, 10 and 12. Patients will be offered a phone number on which study personnel can solve problems and answer queries in relation to psychological ([name]) or pharmacological treatment ([name]).

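### The yes/no cessation outcome is assigned a general linear model, and baseline significance tests are planned after concealed randomisation; both should be replaced, although the unadjusted primary test is barely affected

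*Protocol article*

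**What the plan says.** **Outcome.** Under Sample size the authors write that "we consider the tobacco cessation rate at 1 year follow-up as the main outcome variable". This is a yes/no result for each patient.

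**Model.** Under Analysis strategy the plan is to use the "general linear models of the SPSS 15 statistical package, to analyse the effect of the treatment on the categorical result variables", with the cessation rate named in brackets. The Analysis paragraph of the Abstract repeats this choice. Linear mixed models are reserved for the continuous process variables.

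**Baseline comparison.** The same section opens by comparing the arms "in order to verify that there are no significant differences between the two groups". The method is given as: "For comparisons we will use the Student-t test for continuous variables and the Chi-squared test for categorical variables". The section does not say what would follow from a significant result.

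**Aims that need more than a two-arm test.** Objectives lists two specific aims: factors that predict a good response to topiramate, and possible differences in effectiveness by gender.

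**Therapy groups.** Every patient attends 16 sessions of group therapy. Psychological intervention in both groups states: "The group is made up of 7–12 patients with depression and tobacco dependence, and is led by 2 therapists". The Design section, beside Figure 1, adds: "The evaluation of the treatment outcomes will be performed at patient level and they will be assessed individually". The article does not say whether a therapy group contains one arm or both.

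**The concern.** The plan calls the outcome categorical and, in the same sentence, gives it a model for continuous data. A general linear model treats the residual variance as one constant. A yes/no outcome has variance p(1−p), which changes with the probability being modelled. If generalised linear models were meant, the text still sends the analyst to the wrong procedure, in two places.

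The stake is less the headline p-value than what is built on the model: adjusted estimates, the gender comparison and the predictors of response. There the standard errors rest on a variance assumption that the outcome breaks, and some patients can receive a fitted probability below 0 or above 1.

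The baseline tests are a second stated step that cannot do its job. The article describes a computer-generated sequence, concealed and released by central telephone. Any baseline difference is then due to chance, so a test of whether it is due to chance has a known answer. A significant result does not show that an imbalance matters, and a non-significant one does not show that it is harmless.

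**Working it through.** **Inputs from the article.** n = 90 per arm (N = 180); two-sided alpha 0.05; "we assume that this will be 35% in the control (NST) group"; a difference of 25 percentage points, so 60% or 10% against 35%; therapy groups of 7–12. **Assumed, not in the article:** the intracluster correlation (ICC), taken as 0.01–0.10.

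**The plan's own figure.** For 35% against 60% at 80% power, the usual two-proportion formula gives 62 per arm, or 70 with continuity correction. The stated 90 is matched by 90% power with continuity correction, which is compatible with the stated beta below 0.20. So 90 is not too few, and it does not bear on the choice of model.

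**Step 1: the unadjusted comparison.** A linear model with treatment only is an equal-variance t test on 0/1 data. It is tied to Pearson's chi-squared by

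t² = χ²(N − 2)/(N − χ²).

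The t critical value on 178 df is 1.973 (squared, 3.894). On the chi-squared scale the cut-off is 180 × 3.894/(178 + 3.894) = 3.854, against the usual 3.841. Exact enumeration over all outcomes with 90 per arm gives:

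| True rates | Chi-squared rejects | Linear model rejects |
|---|---|---|
| 35% / 35% | 0.051 | 0.051 |
| 60% / 60% | 0.052 | 0.052 |
| 35% / 60% | 0.918 | 0.918 |
| 35% / 10% | 0.987 | 0.987 |

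The treatment coefficient here is the simple risk difference. With equal arms its squared standard error is [p₁(1−p₁) + p₂(1−p₂)]/(n−1), nearly the ordinary unpooled formula. At 35% and 60% this is √((0.2275 + 0.24)/89) = 0.0725, against √((0.2275 + 0.24)/90) = 0.0721.

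**Step 2: when covariates enter.** The true variance at the article's own rates is 0.10 × 0.90 = 0.09, 0.35 × 0.65 = 0.2275 and 0.60 × 0.40 = 0.24. The largest is 0.24/0.09 = 2.7 times the smallest, yet the model uses one value. Equal arms protect the treatment contrast. They do not protect contrasts between unequal subgroups, such as men and women.

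Fitted values can also leave the range. The self-efficacy scale runs 0–10. Suppose the fitted rate is 35% at a score of 5 and rises by s per point (an assumption). The fitted rate at score 0 is 0.35 − 5s, which is negative once s exceeds 0.07. In an arm quitting at 10%, it is negative once s exceeds 0.02. A treatment-by-gender model alone fits four cell means and stays inside 0–1; the range problem comes with continuous predictors.

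**Step 3: the baseline tests.** About 15 variables can be counted from Table 1 and Secondary variables: age, sex, marital status, education, occupation, social class, Zung, Minnesota, carbon monoxide, cotinine, Fagerström, STAI state, STAI trait, Plutchik and self-efficacy. If independent, P(at least one p<0.05) = 1 − 0.95¹⁵ = 0.54. Several are plainly related, which lowers the figure; if all 15 moved together it would be 0.05.

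**Step 4: therapy groups, in both directions.** 180/12 = 15 and 180/7 ≈ 26, so there are 15–26 groups.
- If each group held one arm: design effect = 1 + (m − 1)ICC, from 1.06 (m = 7, ICC 0.01) to 2.10 (m = 12, ICC 0.10). Ignoring groups gives type I error 2[1 − Φ(1.96/√DE)] = 0.057 to 0.176.
- If each group mixed the arms evenly: the variance of the difference shrinks by about (1 − ICC). Type I error is then 2[1 − Φ(1.96/√(1 − ICC))] = 0.049 to 0.039.

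**The case against.** The best defence is that the primary comparison is sound as it stands. With treatment alone the linear model rejects exactly as often as chi-squared, and it estimates a risk difference directly, which suits an aim of being at least as effective as NST. This stands, and it limits the finding. It does not cover the adjusted, gender and predictor analyses. The article does not fix a model for the last two, but the model it names for cessation is the natural one to be carried over.

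It can also be said that the baseline tests do little harm because no decision hangs on them. That too is largely right. They are a stated procedure without information, not a source of bias by themselves.

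Three stronger readings are tempting, and the article does not support them.
- *The primary type I error is seriously inflated because therapy groups are ignored.* The upper values in Step 4 need single-arm groups and an assumed ICC, and the article gives neither. Its only relevant evidence points the other way: "Study personnel conducting psychological intervention and assessments" are to be masked to treatment, which fits mixed groups better. With mixed groups, ignoring them is slightly conservative. Patient-level evaluation names the unit of assessment; it does not rule out a group term, and such a detail is commonly left to the full plan.
- *The baseline tests stand in for, or will select, covariates.* The text does not say so, and a covariate list may properly sit in the analysis plan.
- *The sample size falls short for want of covariate adjustment.* Approximate power at 90 per arm is already 0.926 for 35% against 60%.

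**Conclusion.** The point holds in limited form. Two stated choices should change: a model for continuous data assigned to a yes/no outcome, and significance tests of baseline variables after concealed randomisation.

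The effect on the unadjusted primary test is negligible (type I error about 0.051). The effect on adjusted and subgroup results is real but cannot be sized from the article, because it depends on covariate effects that the article does not give. The 54% for the baseline tests rests on 15 variables and independence, and is lower where variables are related. The therapy-group issue is conditional, and its direction is unknown until the make-up of the groups is stated. This is a correction worth making before analysis, and it does not threaten the trial's validity.

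**What to change.** 1. **Model.** In Analysis strategy and the Abstract, replace the general linear model for cessation with a binomial (logistic) model for 12-month cessation. Include treatment and a few fixed baseline covariates that the trial already collects: Fagerström, Zung and sex. Report the standardised risk difference with 95% CI. Baseline adjustment can add precision.
2. **Keep the list short.** At 35% in both arms there would be 0.35 × 180 = 63 quitters. At 35% and 10% there would be 31.5 + 9, about 40. Four coefficients (treatment and three covariates) then have roughly 16 or 10 quitters each.
3. **Gender and predictors.** Examine these as treatment-by-covariate interactions in separate secondary models, so that the primary treatment estimate keeps its meaning.
4. **Baseline data.** Report means with standard deviations and percentages by arm, and drop the t and chi-squared tests.
5. **Therapy groups (conditional).** State whether groups mix the arms and record the group number. Run a sensitivity analysis with a group term and a small-sample correction, because with only 15–26 groups uncorrected cluster-robust standard errors tend to be too small.

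**Cost.** Analysis wording, one extra recorded variable and a slightly more complex model. Sample size and visits are unchanged.
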